## Abstract

**Background:**

Albeit exercise is currently advocated as one of the most effective management strategies for fibromyalgia syndrome (FMS); the implementation of exercise as a FMS treatment in reality is significantly hampered by patients' poor compliance. The inference that pain catastrophizing is a key predictor of poor compliance in FMS patients, justifies considering the alteration of pain catastrophizing in improving compliance towards exercises in FMS patients. The aim of this study is to provide proof-of-concept for the development and testing of a novel virtual reality exposure therapy (VRET) program as treatment for exercise-related pain catastrophizing in FMS patients.

**Methods:**

Two interlinked experimental studies will be conducted. Study 1 aims to objectively ascertain if neurophysiological changes occur in the functional brain areas associated with pain catastrophizing, when catastrophizing FMS subjects are exposed to visuals of exercise activities. Study 2 aims to ascertain the preliminary efficacy and feasibility of exposure to visuals of exercise activities as a treatment for exercise-related pain catastrophizing in FMS subjects. Twenty subjects will be selected from a group of FMS patients attending the Tygerberg Hospital in Cape Town, South Africa and randomly allocated to either the **VRET **(intervention) group or **waiting list **(control) group. Baseline neurophysiological activity for subjects will be collected in study 1 using functional magnetic resonance imaging (fMRI). In study 2, clinical improvement in pain catastrophizing will be measured using fMRI (objective) and the pain catastrophizing scale (subjective).

**Discussion:**

The premise is if exposing FMS patients to visuals of various exercise activities trigger the functional brain areas associated with pain catastrophizing; then as a treatment, repeated exposure to visuals of the exercise activities using a VRET program could possibly decrease exercise-related pain catastrophizing in FMS patients. Proof-of-concept will either be established or negated. The results of this project are envisaged to revolutionize FMS and pain catastrophizing research and in the future, assist health professionals and FMS patients in reducing despondency regarding FMS management.

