### Study population and recruitment process

Twenty eligible subjects will be conveniently sampled from the available FMS population currently registered at the Tygerberg Hospital (TBH) Rheumatology clinic and/or attending the monthly FMS group meetings held at the TBH Occupational therapy (OT) department. The rheumatologists and/or occupational therapist working in the TBH Rheumatology clinic and/or OT department will be asked to identify all new or previously diagnosed FMS patients attending the clinic. The principle researcher and research assistant(s) will approach all potential patients personally or telephonically, and invite them to participate in the study. In addition, the clinic's patient database will be manually searched for all potential patients who have been diagnosed with FMS, but no longer attend the monthly meetings or the clinic. All potential patients listed on the database for whom contact details are available will be contacted telephonically and invited to participate in this project.

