
***Study 2: ***On completing baseline scans in study 1, group B subjects (n = 10) will be instructed to complete another set of the PCS and TSK and continue daily activities as normal for the next eight weeks (control group). No other education/treatment/information will be given to group B subjects. Appointments to return to CUBIC for final scans after eight weeks will be scheduled for group B subjects. On completing baseline scans in study 1, one-hour long sessions will be scheduled for group A subjects (n = 10) twice a week for eight weeks (intervention group). During the twice weekly treatment sessions, subjects will be placed in an isolated room and be exposed to visuals of various exercise activities. Visual exposure to exercise activities will be delivered via a VR head-mount display (HMD); namely the eMagin Z800 3DVISOR linked to an ASUS K61IC series laptop. The eMagin Z800 3DVISOR has a highly sophisticated built-in head tracker which allows the user six degrees of freedom in motion [28]. The HMD is placed on the head of the user, blocking off the surrounding environment. The visuals relayed to the HMD via a connected laptop are viewed on two 3D OLED 0.59 inch micro displays, which to the user seem to play as huge as a 105-inch screen. These specific features of the eMagin Z800 3DVISOR enhance the immersion of the user into the virtual environment [28]. Software will consist of an hour-long DVD comprised of various simulated exercise activities. The subject may only be accompanied by a research assistant or translator. The PCS and TSK will be administered before and after each session. Information relating to the feasibility and logistics of the study will be collected from Group A's subjects at the end of the eight-week treatment program.

The PCS and TSK will be administered before and after the eight week time period for both groups. No PCS and TSK scores will be collected during the eight weeks for group B's subjects. At the end of the eight-week study period, both groups will undergo final fMRI scans.

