## Discussion

The premise is if visuals of various exercise activities trigger the functional brain areas associated with pain catastrophizing in FMS subjects; then as a treatment, it can be postulated that graded and repeated exposure to visuals of exercise activities using a VRET program could possibly decrease pain catastrophizing and subsequently decrease fear to movement, essentially improving compliance towards exercise therapy programs among FMS patients. Proof-of-concept for the development and testing of a novel VRET program for exercise-related pain catastrophizing in FMS will either be established or negated. The results of this project are envisaged to revolutionize FMS and pain catastrophizing research and in the future, assist health professionals and FMS patients in reducing despondency regarding FMS management.

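### The protocol promises that proof-of-concept will be established or negated, but with 10 subjects per group a null result in Study 2 cannot negate a treatment effect

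*Protocol article*

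**What the plan says.** The Discussion paragraph of the abstract states: "Proof-of-concept will either be established or negated". The Discussion section at the end of the article says the same at greater length: "Proof-of-concept for the development and testing of a novel VRET program for exercise-related pain catastrophizing in FMS will either be established or negated". Neither place mentions a third possible result.

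The aim is put more modestly in the abstract's Methods: "Study 2 aims to ascertain the preliminary efficacy and feasibility of exposure to visuals of exercise activities as a treatment". The overall project description and the Statistical analysis section also speak of preliminary efficacy.

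On size, the recruitment section says "Twenty eligible subjects will be conveniently sampled". Study procedures gives the split: "group B subjects (n = 10) will be instructed to complete another set of the PCS and TSK" for the waiting-list arm, and "one-hour long sessions will be scheduled for group A subjects (n = 10) twice a week for eight weeks (intervention group") for the VRET arm.

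The Statistical analysis section compares PCS and TSK scores between groups and within subjects, and names a paired t test. It states no significance level, effect size, power or go/no-go criterion.

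**The concern.** To negate a concept is to show that a worthwhile effect is absent. That requires an interval narrow enough to exclude such an effect, and a failure to find a difference does not supply one. The stated conclusion is therefore stronger than a preliminary-efficacy aim, and stronger than 10 subjects per group can normally support.

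The Background presents this project as the step that decides whether a VRET program is developed and tested further. If the either/or sentence is taken at face value, an uninformative Study 2 would have to be filed under one of two headings, and a null estimate would naturally go under the negative one. A useful line of treatment could be dropped on data that do not argue against it.

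**Working it through.** **Inputs from the article.** n = 10 per group (Study procedures); follow-up at eight weeks; PCS maximum 52 (Study outcomes).

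**Assumed, because the article gives no figure.** Two-sided 5% level; 95% intervals; pre-post correlation r from 0.5 to 0.8; PCS SD of 8 to 10 points; no dropout unless stated. Effects are in units of the between-subject SD, with 0.5 SD taken as moderate. The article states no power or sample-size basis, so there is no figure of its own to reproduce.

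**1. Precision.** This step needs no decision rule.
- Unadjusted half-width = t(0.975, 18 df) × √(2/10) = 2.101 × 0.447 = 0.94 SD.
- Baseline-adjusted at r = 0.6: t(0.975, 17 df) × √(2/10) × √(1 − 0.36) = 2.110 × 0.447 × 0.8 = 0.75 SD.
- In PCS points, unadjusted: 0.94 × 8 = 7.5 to 0.94 × 10 = 9.4. Adjusted: 0.75 × 8 = 6.0 to 0.75 × 10 = 7.5.

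If the observed difference were exactly zero, the interval would run from −0.94 to +0.94 SD (or ±0.75 SD adjusted), and a 0.5 SD benefit lies well inside both. To exclude 0.5 SD without adjustment, the estimate would have to be 0.94 − 0.5 = 0.44 SD or more in favour of the control group.

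**2. Miss rate if non-significance were read as negation.** Noncentral t, 18 df, noncentrality d × √(10/2):

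| True benefit | Power | Missed |
|---|---|---|
| 0.5 SD | 18.5% | 81.5% |
| 0.8 SD | 39.5% | 60.5% |
| 1.0 SD | 56.2% | 43.8% |

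Power reaches 80% only at 1.32 SD.

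**3. Sensitivity at a true 0.5 SD benefit.**

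| Rule | Power | Missed |
|---|---|---|
| Baseline-adjusted, r = 0.5 | 23.0% | 77.0% |
| Baseline-adjusted, r = 0.7 | 31.5% | 68.5% |
| Change score, r = 0.7 | 27.7% | 72.3% |
| One-sided 5% | 28.5% | 71.5% |
| Two-sided 10% | 28.8% | 71.2% |
| 8 completers per arm | 15.4% | 84.6% |
| One-sided 20% screen | 60.5% | 39.5% |
| Paired t within VRET arm, r = 0.5 | 29.3% | 70.7% |
| Paired t within VRET arm, r = 0.7 | 44.6% | 55.4% |
| Paired t within VRET arm, r = 0.8 | about 60% | about 40% |

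The between-arm rules at conventional levels miss about 68% to 85%. A lenient screen, or the paired test with high correlation, misses fewer. The paired test, however, measures change within the VRET arm and not the difference from control.

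**The case against.** The sentence is closing prose, and the operative text is restrained: efficacy is called preliminary throughout, and the statement just before the sentence is hedged. That is fair, and it is a reason to treat this as a mismatch between conclusion and design. The sentence still appears twice and is the only account the article gives of what the project will conclude.

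A reader might infer that most moderate true benefits would be wrongly declared negated. The documents do not support that as a flat statement. Nothing in the article equates non-significance with negation, and no significance level is given. The only test of means named is a paired t test, and under that test with high correlation most 0.5 SD effects would be detected. The miss rates hold only under the rule stated with them.

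A reader might also add that several unranked outcomes (PCS, TSK, fMRI) make a false positive easy: 1 − 0.95³ = 14% for three independent outcomes. That figure assumes that any one outcome suffices, whereas the 82% miss rate assumes a single deciding outcome. Under the any-of-three rule the miss rate at 0.5 SD falls to 0.815³ = 54%, so the two harms cannot both be claimed at these sizes. Independence is doubtful too, since PCS and TSK are self-reports from the same subjects. The ranking of outcomes may also be settled in the full protocol, so its absence from the article is not held against the plan.

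Finally, proof-of-concept also covers Study 1, a within-subject fMRI question in all 20 subjects, and feasibility. Two-arm power says nothing about either. This stands, and it limits the point to the Study 2 treatment effect.

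None of this rescues the word negated. The precision argument does not depend on any test or threshold.

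**Conclusion.** The point holds for Study 2 efficacy. With 10 per group, the interval for the between-group difference extends about 0.94 SD either way, or about 0.75 SD adjusted at r = 0.6, so a null estimate leaves a moderate benefit open. Negation would need a result clearly in favour of the control group. If non-significance at two-sided 5% between arms were used as the rule, a 0.5 SD benefit would be missed about 80% of the time, or about 70% with baseline adjustment at r = 0.7.

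The SD-unit half-width rests only on n = 10 per group with all subjects followed up and on the 95% level. The adjusted figures, the miss rates and the PCS-point conversions rest on the stated assumptions. The sample size itself is not criticised, because the article claims no power for it.

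**What to change.** In the abstract's Discussion and in the closing Discussion, replace the either/or sentence with one that allows an inconclusive result.

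For Study 2 efficacy, report the between-group difference in PCS change at week 8 with its 95% confidence interval, and conclude:
- *supported* if the interval excludes zero in favour of VRET;
- *not supported* only if the interval excludes a smallest worthwhile PCS difference that the sponsor states in advance;
- *inconclusive* otherwise.

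Treat TSK and fMRI change as supportive for Study 2. Report the Study 1 fMRI premise and feasibility as separate conclusions, so that the neurophysiological question is not decided by a symptom score.

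**Cost.** No extra subjects or measurements. The sponsor must settle a smallest worthwhile difference before seeing data, so this is slightly more than rewording. *Inconclusive* becomes a likely result. With an illustrative margin of 0.5 SD, *not supported* needs an estimate of at least 0.44 SD in favour of control. If there is truly no effect, that happens about one time in six (0.44 / 0.447 = 0.98 standard errors). This reflects what 20 subjects can show.

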**Trial registration:**

PACTR201011000264179

## Background

Fibromyalgia syndrome (FMS) is arguably one of the most complex chronic pain conditions to manage [1]. Characterized by widespread musculoskeletal symptoms and functional disability; FMS is a debilitating condition which affects millions of people around the world [1]. The significant impact FMS has on quality of life, society, industry, healthcare systems and state budgets has rendered FMS a global public health concern [2,3].

Albeit the recent recognition of FMS as a legitimate condition, the exact aetiology of FMS remains unknown [1,4]. Finding effective management strategies for FMS thus continues to frustrate patients and health professionals [4,5]. Largely based on symptomatic relief, the management of FMS usually consists of a combination of pharmacological and non-pharmacological therapies [4,5]. With no one intervention found to be superiorly more effective than the next, FMS management programs are typically individualized to the patient's needs and progressed accordingly [4,5]. Nonetheless, since most FMS patients display some degree of functional disability and muscle deconditioning, the current international consensus is that exercise therapy should at least be a key component of most FMS management programs [6,7]. Evidence from clinical trials has reported that exercise therapy can be beneficial to most FMS patients and is effective in reducing functional disability and FMS symptoms [8,9]. For this reason, exercise therapy is currently one of the most advocated management strategies for FMS [9,10].

The implementation of exercise therapy as a management strategy for FMS in reality is however significantly hampered by poor compliance to exercise programs among FMS patients [11]. Poor compliance towards exercise and other treatments is a common trait among FMS patients and is the primary factor contributing to the chronicity and accelerated deterioration of the condition [11]. A key predictor of poor compliance towards exercise or activity has recently been identified as pain catastrophizing; a cognitive strategy broadly defined as "an exaggerated negative orientation towards actual or anticipated pain experiences" which significantly contributes to the maintenance of chronic pain [12,13].

Currently, the role of pain catastrophizing is believed to be more pronounced in FMS than in other rheumatologic conditions and is recognized as a barrier to the healthy development of psychological and physical functioning among FMS patients [13,14]. Of concern is that in FMS patients, the presence of pain catastrophizing leads to fear-avoidance behaviours which often results in attrition of physical activity [14]. Inactivity is particularly detrimental in FMS and typically leads to further complications such as weakening of the musculoskeletal system, increased pain, increased fatigue and functional disability [8-10]. To date, research has focused on identifying the predictors of poor treatment compliance in FMS, but to our knowledge there is no research into management approaches aimed at addressing these predictors and poor compliance to exercise programs in FMS. The inference that pain catastrophizing and subsequent fear-avoidance behaviours may influence the compliance of FMS patients towards exercise programs, justifies considering the alteration of pain catastrophizing in the management of FMS [14,15].

Evidence suggests that cognitive-behavioural therapy, specifically exposure therapy, may be useful in the alteration of pain catastrophizing [15-18]. Exposure therapy involves exposing an individual to a task or movement that he/she fears, until the emotion of fear is alleviated and disassociated from that particular task or movement [19]. In improving compliance towards exercise programs in FMS, the use of exposure therapy is based on the hypothesis that if patients are repeatedly exposed to visuals of exercise activities or situations that they report to catastrophize, pain catastrophizing levels should decrease over time. The decrease in pain catastrophizing should ideally lead to a decrease in fear-avoidance behaviours, which could fundamentally increase compliance to the recommended exercise programs. With improved compliance to exercise programs, FMS patients may be able to realize the true benefits of exercise and enjoy an improved quality of life.

Although exposure therapy is traditionally conducted during real situations (in vivo exposure therapy) or during an imagined situation (imagined exposure therapy), more recent innovations indicate that exposure therapy can also be administered via virtual reality technology, namely *virtual reality exposure therapy *(VRET) [20,21]. VRET is a type of exposure therapy in which the user can be immersed into a computer-generated environment via a head-mount display and exposed to a simulation of a specific feared situation [20,21]. Contrary to other types of exposure therapy, VRET seems ideal for conditions where the real situations are inaccessible or costly (in vivo exposure) or individuals find it difficult to imagine various situations (imagined exposure therapy) [20,21]. To date, VRET has successfully been used for other forms of phobias, such as fear for spiders and flying, but has never been used in the treatment of fear of movement/exercise, nor pain catastrophizing in chronic pain conditions.

The previous postulation that imagined exposure therapy may effectively reduce pain catastrophizing in FMS patients makes the investigation of VRET as a treatment for pain catastrophizing in FMS a plausible option [17]. However, since no VRET program for the treatment of pain catastrophizing in FMS patients currently exists; preliminary steps are required prior to the development and testing of such a program. Initially, it has to be ascertained if visual exposure to catastrophized exercise activities cognitively triggers the functional brain areas associated with pain catastrophizing. The premise is that if visual stimuli of the catastrophized exercise activities cognitively trigger pain catastrophizing in the associated functional brain areas; graded and repeated exposure to visuals of the catastrophized exercise activities using a VRET program could possibly decrease pain catastrophizing and subsequently decrease fear to movement, essentially improving compliance towards exercise therapy programs among FMS patients. If the results of this proof-of-concept study are positive, this scientific breakthrough in FMS research will enable FMS sufferers to engage in beneficial physical activity without fear and possibly improve their quality of life. The following protocol presents the details of a project which aims to provide proof-of-concept for the further development and testing of a novel VRET program as treatment for exercise-related pain catastrophizing in FMS patients.

## Methods

Ethical approval for this study was obtained from the Health Research Ethics Committee of the Stellenbosch University during July 2010. Permission to conduct the study at the various study centres was granted by the various departmental heads. All eligible subjects will be required to read and sign an informed consent form before participating in this study. A unique study identification number/code will be allocated to subjects as they are entered into the study, thereby maintaining anonymity of all study participants. Confidentiality of participant's information will be maintained throughout the study process by storing the study data in a locked facility accessible only to the study personnel.

### Description of the overall project

The proposed project will consist of two interlinked experimental studies: Study 1 and Study 2.

**Study 1 **will incorporate an observational within-subject study design and aims to ascertain the neurophysiological changes occurring in the functional brain areas associated with pain catastrophizing when catastrophizing FMS patients are exposed to various visuals of exercise activities. Functional magnetic resonance imaging (fMRI) will be used to observe these neurophysiological changes within the associated functional brain areas. Study 1 will be conducted at the Cape Universities Brain Imaging Centre (CUBIC) situated at the Stellenbosch University's Tygerberg medical campus in Cape Town, South Africa (SA).

**Study 2 **will incorporate a quasi-, within-subject/between-groups experimental (pre- and post-, with/without treatment) study design and aims to ascertain the preliminary efficacy of visual exposure to exercise activities on pain catastrophizing in FMS patients. Clinical improvement in pain catastrophizing will be measured using objective and subjective outcome measures. The feasibility of using visual exposure to exercise activities as a treatment for pain catastrophization experienced by FMS patients in terms of: 1) time taken to administer; 2) ease of use; 3) safety of administration; 4) participant acceptability; and 5) participant opinion/thoughts of the intervention, will also be ascertained. Study 2 will be conducted at the Body in Motion analysis lab at the Stellenbosch University's Tygerberg medical campus in Cape Town, SA.

It is envisaged that the data collection period of the project will commence in June/July 2011 and be completed by September/October 2011.

